### 2.3. Dietary Interventions

Both diets (MD and low-fat diet) will be implemented by dietitians/nutritionists from each center. First of all, the total energy requirements of adolescents will be calculated by using the Molnar equation [41], and the level of physical activity will be obtained from the validated Physical Activity Questionnaire for Adolescents (PAQ-A). Afterwards, a caloric restriction of 20% will be applied to design a personalized diet for each obese individual (BMI ≥95th percentile) [42], while caloric restriction will be carefully evaluated for each individual with great overweight (BMI ≥90 to <95th percentile). For ethical issues, adolescents will not be conscious about caloric restriction of their diet, but only about dietary recommendations to follow the specific diet. In addition to the volunteer’s energy requirements, diets will take into account their food preferences and culture.

A weekly meal general plan, including portion sizes and a list of food equivalents will be provided to participants in both groups, so they could adapt and personalize their menus. The dietary prescription will be also easily accessible by both adolescents and their parents through an educational web-application developed by UNIPR partner. In addition, parents will be provided with a daily recipe to facilitate the adherence to the dietary prescription as well as to increase their culinary skills and the engagement in the project. Moreover, in each country, some recipes will be traditional of another country, i.e., a Spanish recipe in Italy or an Italian plate in Portugal.

(1)The MD will be based on a high consumption of unsaturated fat from vegetable sources (extra virgin olive oil and nuts) and minimally processed plant foods (vegetables, fruits, nuts, whole grains and legumes), low consumption of meat (especially red and processed meats) and sweets, and moderate consumption of fish and dairy products (mainly yogurt and cheese) [6,43]. Accordingly, this diet will provide a high amount of mono and polyunsaturated fatty acids, fiber, and phenolic compounds [44]. The MD will be based on the one proposed as MD in the PREDIMED study [45], providing 40–45% of energy from carbohydrate, 35–40% from fat, and 15–20% from protein. Special attention will be paid to the benefits of whole and minimally processed foods, traditional food vs. fast food, and seasonal products. Within the MD pattern, the intervention group (MD) will consume a sourdough bread and 3 specific foods from the Mediterranean basin with proven healthy effects (pomegranate juice, chickpeas/hummus, and mixed nuts) (Table 1).

In summary, adolescents in the MD group will replace the intake of conventional bread by sourdough bread consumption (2 servings of 50–60 g daily), they will incorporate into their diet chickpeas (2 servings of 150 g/week chickpeas, a minimum of one of them being hummus), while they will consume at least another serving of legumes, which can be chickpeas or another legume, and will consume pomegranate juice (4 servings of 200 mL/week) and mixed nuts (4 servings of 30 g/week). The sourdough bread will be a multigrain leavened with Rebola sourdough, which has been previously shown to elicit a lower increase in postprandial blood glucose levels and to decrease the inflammatory marker MCP-1 in rats when compared to a conventional white bread [35]. The squeezed pomegranate will be a single-strength juice. It will be squeezed with the arils, seeds, and inner and outer shell in order to get the important polyphenols existing in the fruit. Chickpeas are a popular pulse rich in protein and dietary fiber and will be consumed boiled and as hummus (paste of chickpeas, tahini, olive oil, lemon, and herbs).

(2)The low-fat diet (control diet) consists of a restricted consumption of fats. This diet will be based on the one proposed as low-fat diet in the PREDIMED study [45], and it will provide 55% of energy from carbohydrate, 25–30% from fat, and 15–20% from protein. The low-fat diet is the most used diet for obesity treatment in adolescents [42]. This group will not receive any additional specific food by the researchers.

Volunteer’s compliance with the dietary prescription will be assessed by means of self-reported weekly food checklists, 3-day dietary records, and selected biomarkers of food intake.

### 2.4. Implementation of the Motivational Interview Technique

Before beginning the intervention, a personalized dietary advice (30-min session) to each participant including recommendations on the desired frequency of intake of specific foods and general recommendations about performing physical activity will be delivered by dietitians/nutritionists by using the psychological “motivational Interview” technique [48]. The motivational interview will have a standardized internal protocol that will follow the dietitians/nutritionists of the 3 each enrolment centers.

In the first session, the attendance of parents, mentors, or caregivers will be recommended, as they can strongly encourage their children and help the adolescents understand and follow the lifestyle recommendations. Especially, parents can help with cooking and with food purchase.

### 2.5. Educational Web-Application

The adolescents of both groups and their parents will have access to an educational web-application to be used during the intervention, where they can learn about health, nutrition, and food in general, how the right food choices positively impact on health, in addition to providing information on sustainability issues and the link between health and sustainability. The application will be developed as a cross-browser web-application with responsive design, so it will be available for both desktop and mobile devices. The application will be accessible at a specified secure URL and will require a username and a password to enter in the main page. The URL and the personal username and password will be provided to each participant at the beginning of the intervention period. Internet will be needed to use the application, independently if they use a computer, a smartphone, or a tablet. To ensure the validation and usability of the web-application, a pilot study will be performed in Italy with teenagers aged 13–17 years. The web-application will be intended for two final user typologies, namely the adolescent participant user and the parent user. For each one of the two users, specific contents will be available on the basis of the intervention group to which they will be assigned (MD or control group). The application will be designed to be used independently in Spanish, Italian, and Portuguese.

For the adolescents allocated to the MD group, the application will also include specific contents about MD, including information about pomegranate juice, hummus/chickpeas, mixed nuts, and sourdough bread.

To help engage participants, a “learning-through-playing” approach will be used, combining together educational materials and games [49], such as group-specific educational contents, group-specific tips of the day, group-specific quizzes, and group-specific recipes of the day. Among the group-specific educational contents (MD or control diet), one topic will be available per each intervention week (16 weeks) with weekly release. In addition, a “welcome” content will be also available at the beginning of the study. Based on the topic of the week, the quiz game will be composed by 15 multiple-choice questions per week: 2 questions per day plus one final general question. The user should answer the right option to move to the next question/level (only two attempts will be available for each question per day), and every week, a new level will be available. To increase participants’ engagement, a scheme with badges/achievements will be available. Adolescents will have access to the application every day to get the “tip of the day”, which is a short and easy “take-home message” defined to improve their food literacy and play with the quiz game. In addition, the application will be used to deliver the personalized dietary plan designed by a dietitian/nutritionist and to collect data during the intervention study by means of 3-day food diaries and questionnaires. Information on healthy diet and nutrition will also be provided to the parents through the app to help them support their kids. In addition, parents will be able to browse the “recipe of the day” to find everyday a new recipe helping them to prepare tasty and nutritious meals, and they will also have access to the weekly educational contents and to the diet of their children.

### 2.6. Manufacturing and Distribution of the Mediterranean Basin Foods

The sourdough bread will be manufactured by NOVAPAN. Afterwards, NOVAPAN will distribute the sourdough bread to the three enrollment centers. These breads will be sent several times to each institution during the study, will be stored at the centers at −20 °C, and will be provided periodically by the researchers of each center to the adolescents (and/or parents of the adolescents) allocated in the MD group. The breads will be provided to the volunteers at no cost, and an extra amount of breads will be given for the rest of family in order to increase compliance.

Chickpeas/hummus and pomegranate juice will be sent by Shikma Field Crops to each center and will be provided to the MD group. Chickpeas/hummus and pomegranate will be sent several times during the study. Hummus and pomegranate will be delivered in refrigerated conditions, while chickpeas will be delivered cooked and canned.

Walnuts, almonds, and hazelnuts will be distributed by the company COSELVA (La Selva del Camp, Tarragona, Spain) to the different centers. The nuts will be packaged by COSELVA in an individual package containing 10 g for each nut (walnuts, almonds, and hazelnuts).

Moreover, extra virgin olive oil (EVOO) will be provided to the MD group in order to ensure that this group uses this type of fat for cooking and dressing. EVOO will be distributed by COSELVA to the different centers.

### 2.7. Outcomes

The primary outcome is the BMI z-score, which is a standardized measure of BMI based on specific age and sex [50,51]. The effectiveness of the intervention will be evaluated by comparing the BMI z-score between the control (low-fat diet) and intervention (MD) groups.

The secondary outcomes are:MD adherence, using the KidMed questionnaire [19]Physical activity, using Physical Activity Questionnaire for Adolescents (PAQ-A) [52]Dietary intake and habits:
○3-day dietary records [53]○Food frequency questionnaire (FFQ) of the Helena study [53]
Nutritional knowledge, using the NK Helena questionnaire [54]Quality of life, using the kidscreen-27 Index [55]Sociodemographic data, using the Health Behavior in School Age Children (HBSC) socio-demographic questionnaire [56]Anthropometric data: weight, height, BMI (weight/height^2^), body composition using bioimpedance, waist circumference (WC), and waist–hip ratio (WHR)Blood pressureBiochemical variables, gut microbiota composition, and metabolomics in urine, blood, and feces

All outcomes are presented and summarized in Table 2.

The questionnaires will be used to collect data on the habits and knowledge of the participants in different visits. These data will be collected through the app and then combined with anthropometric and food intake data to assess possible associations among these variables.

At visit (V)1, V2, V3, and V4, the subjects will attend the partner center in over-night fasting conditions to evaluate anthropometric parameters, dietary intake, physical activity, and blood pressure. At V1 and V3, feces, blood, and morning urine will be collected to perform the analyses of microbiota and gut-derived metabolites; food intake biomarkers and phenolic metabolites; circulating levels of glucose and blood lipid profile, biomarkers of insulin resistance, adipose tissue function, inflammation, oxidative stress, and cardiovascular risk, and advanced glycation end products (AGEs). In addition, the lipid profile of the erythrocyte membrane will be assessed at V1 and V3. Data collected at V4 will be used to investigate if the intervention will have changed medium-term dietary habits, having a medium-term impact also on blood pressure and anthropometric parameters. Additionally, for female adolescents, information about their menstrual cycle will be recorded in each visit. Table 3 shows the schedule of each visit, which will follow the same timeline for each enrollment center.

### 2.8. Sample Size

According to the sample size calculations based on differences in BMI z-score (primary outcome) between groups (0.2 difference with 80% power; two-tailed α: 0.05; standard deviation: 0.5; dropout rate: 20%), a total of 240 volunteers from three Mediterranean countries (Spanish, Portugal and Italy) will be recruited for this study (80 participants per country) after obtaining the approval of the Ethics Committees of each recruiting center and the written informed consent from parents and from subjects.

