## 2. Materials and Methods

### 2.1. Study Design and Setting

The overall design of the study is represented in Figure 1. The MED4Youth study is a multicenter single-blinded randomized controlled clinical trial with obese and overweight adolescents (13–17 y) from Italy, Portugal, and Spain, in which an MD-based intervention will be compared to a traditional low-fat diet intervention. The three centers involved in the study obtained the approval of the Ethics Committee of each institution: (1) Eurecat (study coordinator): Institut d’Investigació Sanitària Pere i Virgili (Ref. CEIM: 210/2020); (2) UNIPR: Area Vasta Emilia Nord (AVEN) Ethical Committee (pre-approval Ref. Prot. 28638); (3) UC: Ethics Committee of Centro Hospitalar e Universitário de Coimbra and Portuguese National Data Protection Commission (Ref. CHUC-197-20). MED4Youth study was registered at ClinicalTrials.gov (NCT04719052). The protocol conformed to the Helsinki Declaration and Good Clinical Practice guides of the International Conference of Harmonization. This study followed the CONSORT criteria.

According to the sample size calculations, a total of 240 volunteers from Italy, Portugal, and Spain will be recruited for this study (80 participants per country).

The Spanish subjects will be recruited by Eurecat in the province of Tarragona, the Portuguese subjects will be recruited by the Hospital Pediátrico de Coimbra, and the Italian subjects will be recruited by the Pediatric Clinic of the Maternal and Child Department of the Parma University Hospital. The 80 individuals recruited in each country will be randomly assigned to either a MD group (n = 120, n = 40 per country), which will be instructed to follow an MD that will incorporate sourdough bread, hummus, pomegranate, and mixed nuts, or a Control group (n = 120, n = 40 per country), which will be assigned to a standard low-fat diet. The intervention duration is 4 months for each participant, including 3 visits. A follow-up visit after 4 months from the end of the intervention will be carried out.

The randomization code will be computer-generated using software (Geoffrey C. Urbaniak and Scott Plous, Lancaster, PA, USA). Furthermore, the unit responsible for the randomization will be separate from the study researchers.

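### The stated 240 allows for about 17% dropout, not 20%: for an unadjusted comparison, section 2.8's own inputs need about 246 to 250, and 240 gives about 79% power

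*Protocol article*

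**What the plan says.** Section 2.8 (Sample Size) gives all the inputs in one sentence. The calculation rests on "differences in BMI z-score (primary outcome) between groups (0.2 difference", with "0.2 difference with 80% power", "two-tailed α: 0.05" and "standard deviation: 0.5; dropout rate: 20%), a total of 240 volunteers". Section 2.1 (Study Design and Setting) repeats the total: "According to the sample size calculations, a total of 240 volunteers from Italy, Portugal, and Spain will be recruited". It splits the total equally, 120 per arm and 40 per arm in each country.

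The article does not give the number of completers required, the formula used for dropout, the test behind the calculation, or whether the SD of 0.5 belongs to end-point values, changes from baseline or residuals. Section 2.9.1 plans an ANCOVA of change from baseline at the end point, adjusted for age, sex and the baseline value.

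**The concern.** The sentence lists its premises and its result, so the result can be checked without any outside figure. The total of 240 is what one gets by adding 20% to the completers needed. An allowance for 20% loss has to be made by dividing by the proportion retained, 0.80, because the loss applies to everyone randomised and not only to the completers.

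This is the only justification given for the size of the trial, and it concerns the primary outcome. A reader who takes the 20% at face value would believe that attrition up to that level leaves 80% power. If attrition fell between about 17% and 20%, the trial report could call it within plan although, by the plan's own calculation, power was already below 80%.

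**Working it through.** **Inputs (section 2.8):** difference 0.2; SD 0.5; two-sided alpha 0.05 (z = 1.960); power 80% (z = 0.842); dropout 20%. **Allocation (section 2.1):** 120 per arm.

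**1. Completers needed per arm, unadjusted two-sample comparison**
- Normal approximation: n = 2 × (1.960 + 0.842)² × (0.5/0.2)² = 98.1, so 99.
- Exact t test: power is 79.97% at 99 and 80.4% at 100, so 100.

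**2. Reproducing the stated figure**
- 100 × 1.2 = 120 per arm, 240 in total. This matches exactly.
- With the normal approximation, 99 × 1.2 = 118.8, so 119 per arm and 238 in total. This is close but not exact.

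**3. Number to randomise if 20% are lost, n/(1 − 0.20)**

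| Basis | Per arm | Total | Above 240 |
|---|---|---|---|
| Normal, inflated before rounding | 98.11/0.8 = 122.6, so 123 | 246 | 6 |
| Normal, rounded first | 99/0.8 = 123.75, so 124 | 248 | 8 |
| t test | 100/0.8 = 125 | 250 | 10 |

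**4. What 240 delivers at 20% loss**
- Completers: 120 × 0.80 = 96 per arm, 192 in total.
- Power at 96 per arm, standardised difference 0.2/0.5 = 0.4: 78.7% (noncentral t) or 79.1% (normal).

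**5. Dropout that 240 can bear at 80% power**
- t test: 1 − 100/120 = 16.7%.
- Normal: 1 − 99/120 = 17.5%.

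**6. Planned baseline-adjusted analysis**

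This step rests on two assumptions that the article does not state: that 0.5 is the SD of the end-point value, and a value for its correlation r with baseline. The residual SD is then 0.5 × √(1 − r²). With 96 per arm (t test):
- r = 0.3: residual SD 0.477, power about 82%.
- r = 0.5: residual SD 0.433, power about 89%.
- 80% power needs a residual SD of about 0.492, which corresponds to r of about 0.18.

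**The case against.** The best case for leaving the sentence alone has three parts.

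*The gap is trivial.* It is about one percentage point. An SD of 0.492 in place of 0.5 would close it, and 0.5 and 20% are round planning values whose uncertainty is larger than the error. This stands, and it sets the weight of the point. It does not make the sentence correct, since every way of rounding gives more than 240.

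*The planned analysis is not the unadjusted comparison.* If 0.5 is the SD of the end-point value, a baseline correlation of about 0.18 is enough to restore 80%. If 0.5 is the SD of the change, adjusting for baseline can still only reduce the residual variance, apart from a negligible loss of degrees of freedom. Only if 0.5 is already the residual SD does power stay at about 79%. This also stands, and it is why the shortfall is claimed for an unadjusted comparison only. But section 2.8 neither claims this gain nor gives a correlation, so it cannot support the 80% as written.

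*Analysis is by intention to treat, so dropouts are kept.* Section 2.9.1 does name that principle. Section 2.8 nevertheless makes an explicit dropout allowance, so its own calculation treats dropouts as lost.

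Three stronger readings are tempting and are not supported. A reader might infer that the trial is underpowered in a way that matters; the figures above do not show that. A reader might add that the planned removal of outliers by Grubbs' test (section 2.9.1) lowers power further; but removing extreme values also lowers the observed SD, so the net effect on power is not established, and it is no part of this point. A reader might also take the multiplication by 1.2 as proven. It fits exactly, but the article does not state its formula, and 240 could also reflect rounding to an even split over three countries.

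**Conclusion.** The point holds as a minor arithmetic correction. Under section 2.8's own inputs, and for an unadjusted two-sample comparison with dropouts treated as lost, 240 randomised does not give 80% power at 20% dropout. It gives 78.7% to 79.1%, and 80% is kept only up to 16.7% to 17.5% dropout. The numbers are certain given those inputs. What remains open is the power of the analysis actually planned, because the article does not say what the SD of 0.5 refers to and gives no baseline correlation. That power may be at or above 80%.

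**What to change.** Keep 240 and change one sentence in section 2.8, in either of two ways:

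- Restate the allowance, for example: *240 randomised gives 80% power for an unadjusted comparison with up to about 17% dropout, and about 79% with 20%.*
- Or say what the SD of 0.5 refers to, and give the power of the planned baseline-adjusted ANCOVA with 96 per arm together with the baseline correlation assumed and its source. If 0.5 is the SD of the end-point value, that is about 82% at a correlation of 0.3 and about 89% at 0.5.

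Neither version needs extra participants or any change in conduct. The first makes the stated figure slightly less favourable. The second requires the sponsor to commit to a correlation that it can justify.

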### 2.9. Statistical Analyses

#### 2.9.1. Univariate Data Analysis

Data will be expressed as mean ± standard deviation (SD). Grubbs’ test will be used to detect outliers, which will be discarded before subsequent analyses. The normality of variables will be assessed by the Kolmogorov–Smirnov test. Non-parametric variables will be log transformed. Differences in baseline characteristics between subject groups will be analyzed by analysis of covariance (ANCOVA), in which dietary intervention group assignment (G) will be used as a fixed factor and the variables age and sex will be included as covariates. Analyses will be made by intention-to-treat. An ANCOVA model will be used to analyze the data at the end point. The anthropometric and biochemical parameters (changes from baseline) will be used as dependent variables, dietary intervention (MD; low-fat diet) will be included as fixed factor, and the variables age and sex, as well as baseline values, will be included as covariates. Within each group (MD and low-fat diet), changes from baseline will also be analyzed at the end point by a paired *t* test. Within each group (MD and low-fat diet), changes from baseline will also be analyzed considering the different time points using a general linear model for repeated measures. All statistical analyses will be performed with SPSS Statistics (SPSS, Inc., Chicago, IL, USA), setting the level of statistical significance at bilateral 5%. For metagenomics analysis, the non-parametric Mann–Whitney U test will be performed to elucidate pairwise differences on bacteria relative abundance among dietary groups. The Benjamini–Hochberg method will be used to adjust P values for multiple testing considering a 5% false discovery rate. Statistical analyses will be conducted with open-access STAMP software.

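### Grubbs-flagged values are discarded without evidence of error and before any log transform, which conflicts with the stated intention-to-treat analysis and removes valid high biomarker values

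*Protocol article*

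**What the plan says.** Section 2.9.1 (Univariate Data Analysis) sets out the data handling in this order:

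1. Grubbs' "test will be used to detect outliers, which will be discarded before subsequent analyses".
2. "The normality of variables will be assessed by the Kolmogorov–Smirnov test".
3. "Non-parametric variables will be log transformed".
4. Later in the same paragraph: "Analyses will be made by intention-to-treat".
5. For the end-point ANCOVA: "The anthropometric and biochemical parameters (changes from baseline) will be used as dependent variables".

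Section 2.7 states: "The primary outcome is the BMI z-score". The outlier rule does not exempt it. The rule is not limited to measurement or entry errors, and the article mentions no analysis with the flagged values kept. Nothing elsewhere in the article qualifies it.

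**The concern.** There are two problems, and both lie in the text itself.

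**Principle.** Intention-to-treat means that randomised participants are analysed as randomised with the data they provided. A rule that drops a value because it is large or small is a post-randomisation exclusion that depends on the outcome. The same paragraph states both.

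**Order.** Grubbs' test takes its critical value from a normal sample. On the raw scale of a right-skewed marker, the upper tail will look like outliers when it is ordinary data. The plan expects some variables to be non-normal, since it provides a log transform for them, but it applies that remedy after the deletion. Table 2 lists several markers that could plausibly be right-skewed, such as CRP, IL-6, TNFα, leptin, TMAO and blood lipids.

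At stake are the completeness of the main analysis, the means and variances of the biomarkers and, under some ways of applying the rule, the error rate of the group comparison.

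**Working it through.** **Sample size used.** Section 2.8 gives "0.2 difference with 80% power", "two-tailed α: 0.05", SD 0.5 and 20% dropout. A two-sample t test needs 99.1, so 100 per arm; 100 × 1.2 = 120 per arm, or 240, which is the plan's figure. The checks below use 240 × 0.8 = 192 completers, 96 per arm.

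**Test.** G = max|x − mean| / s, two-sided at 5%. The critical value is 3.59 for n = 192 and 3.37 for n = 96. The article does not state the level, the number of passes, or whether the test is pooled or by arm, so these are varied.

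**(a) Skewed biomarkers.** The article gives no distributions; lognormal data with log-SD 0.5 to 1.0 are an assumption. Taking log-SD 0.8 and median 1:

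- mean = exp(0.8²/2) = 1.377
- SD = 1.377 × √(exp(0.64) − 1) = 1.304
- cut-off = 1.377 + 3.59 × 1.304 ≈ 6.06
- on the log scale, ln(6.06)/0.8 ≈ 2.25 SD above the centre
- upper tail beyond 2.25 SD ≈ 1.2%, and 192 × 0.012 ≈ 2.3 values

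Two or three perfectly ordinary values are therefore expected beyond the cut-off even before any repetition shrinks the SD. Simulation with 192 values and no true outliers:

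| Log-SD | Data sets losing at least one valid value | Deleted, single pass (change in mean) | Deleted, repeated (change in mean) |
|---|---|---|---|
| 0.5 | about 90% | 0.9 (−1%) | 2.5 (−3%) |
| 0.8 | about 99% | 1.0 (−3%) | 5.7 (−11%) |
| 1.0 | about 100% | 1.0 (−5%) | 8.5 (−20%) |

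If the same data are logged first, only about 0.04 to 0.06 values per 192 are flagged.

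**(b) Type I error.** ANCOVA of log V3 on log V1 with no group effect, log-SD 0.8 and 1.0, assumed V1–V3 correlation about 0.6:

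- no deletion, or pooled deletion: about 5%
- single pass within arm: about 6%
- repeated within arm: about 8 to 9%

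**(c) BMI z-score, normal changes.** With a uniform shift of 0.2 and SD 0.5, about 0.05 values are deleted on average. The effect stays at 0.20 and power at 78%.

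**(d) BMI z-score, responder subgroup (assumed).** If 5% of the MD arm respond by an extra 1.0 z, the true effect is 0.05 × −1.0 = −0.05.

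| Change SD | Distance of a responder from the rest | Estimate after deletion |
|---|---|---|
| 0.25 (assumed) | 1.0/0.25 = 4 SD | −0.02 to −0.04, depending on scope and passes |
| 0.35 (assumed) | 1.0/0.35 ≈ 2.9 SD | about −0.04 |
| 0.5 (section 2.8) | 1.0/0.5 = 2 SD | moves by about 0.003 |

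With 10% responding (true effect −0.10) and SD 0.25, the estimate is about −0.07 if pooled and repeated, and about −0.09 if repeated within arm or done in a single pooled pass.

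The ratio of the responder shift to the SD is what matters. At SD 0.5 a loss appears only if the assumed shift is far larger: with 5% shifted by 2.0 z (again 4 SD), repeated deletion takes −0.10 to about −0.05 pooled, or −0.06 by arm.

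**The case against.** The strongest reply is that the harm to the primary result is small. For roughly normal BMI z-score changes the rule deletes almost nothing, and at the plan's own SD of 0.5 an extra response of 1.0 z is not extreme enough to be removed. That stands. A reader might infer from the rule that it strips genuine responders from the primary analysis and biases the effect and its standard error. The article does not support that as a flat statement: it describes neither a heavy tail nor a responder subgroup, and gives no change SD below 0.5.

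A second reply is that the larger figures come from different readings. The inflated type I error needs repeated deletion within arm, whereas the largest responder loss needs repeated pooled deletion. No single reading gives both. Pooled screening also fits better with the blinded analysts described in section 2.1 and the Discussion. This stands too, so each figure must carry its condition.

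A third reply is that discarding values is not the same as dropping participants or moving them between arms, so to call the rule wholly irreconcilable with intention-to-treat goes too far. That is fair as to degree. It does not remove the conflict, because valid data of randomised participants are still excluded according to their size.

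Nor can the matter be left to an unseen analysis plan. Level, passes and scope could be settled there, but the discard rule and its place before the transform are stated here, and an analysis plan that kept the values would have to contradict the article.

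**Conclusion.** The concern holds in a limited form and should be fixed. Two parts rest on the text alone: values are discarded without evidence of error, against the stated intention-to-treat principle, and a test that assumes normality is placed before the normality check and the log transform.

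The practical damage falls mainly on right-skewed secondary biomarkers, where the loss of valid high values is close to certain under log-SDs of 0.5 to 1.0. Those log-SDs are assumptions. How large the loss is depends mostly on whether the test is repeated.

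General inflation of the type I error is not shown; it is material only under repeated within-arm deletion. Bias in the primary comparison is a risk that depends on a heavy tail or on responders lying several SDs from the rest, and it is negligible otherwise. The sample size is not affected.

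**What to change.** Replace the outlier sentence in section 2.9.1 with text to this effect:

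- All recorded values are retained in the main analysis.
- Extreme values are queried against source, blind to group, and only confirmed measurement or transcription errors are corrected or set to missing.
- Right-skewed biomarkers are log-transformed before any outlier screening (for example, log V3 with log V1 as covariate).
- An analysis that excludes statistical outliers is reported as a sensitivity analysis only, with its level, number of passes and scope (pooled or by arm) fixed in advance.

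The cost is one paragraph of analysis text and a blinded data-query step. No new data or participants are needed.
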